### Data collection

Three questionnaires will be set up via “Wenjuanxing”, a Chinese online platform providing survey functions. These questionnaires were evaluated by a panel of experts and were revised based on their suggestions and a pre-survey conducted among 30 college students. The protocol including the questionnaires was revised based on information collected in the pre-survey. Table 2 depicts informative to be collected in the study.

At Phase I, Questionnaire A will be used to collect socio-demographics and background information of both college students and their grandparents. Purpose-designed questions have been developed to examine college students’ knowledge about COVID-19 vaccination in older adults. Besides, the Health Belief Model (HBM) and the Theory of Planned Behavior (TPB) model, both of which have been widely used in the context of vaccination, are also included in Questionnaire A to explain and predict college students’ willingness to persuade grandparents to receive the COVID-19 vaccine [26, 27].

At Phase II, Questionnaire B and Questionnaire C will be respectively used to collect information on COVID-19 vaccination status, attitude towards and intention to COVID-19 booster dose of participants’ grandparents at the beginning and end of this phase.

In three questionnaires, we provide clear options for objective questions. Several quality-control questions will be included in our study questionnaires, and the consistency of answers will be examined by trained investigators. All investigators have completed standard operating procedure training and data management training. For subjective questions, traditional five-point Likert’s scales are used to assess college students’ knowledge about COVID-19 and COVID-19 vaccination in older adults, HBM, TPB, grandparents’ attitude towards and intention to get COVID-19 booster dose (Additional files 1 & 2). Of note, in order to ensure the reliability and validity, all the Likert’s scales mentioned above are adapted from previous studies [18, 28].

**Table 2 Tab2:** Summary of information to be collected

Population	Modules	Questionnaire code(s)
College students	Socio-demographics	A
	Knowledge about COVID-19 vaccination in older adults	
	HBM predictors for willingness to persuade grandparents to get COVID-19 vaccination	
	TPB predictors for willingness to persuade grandparents to get COVID-19 vaccination	
	Willingness to persuade grandparents to get COVID-19 vaccination	
	Willingness to participate in Phase II	
Grandparents	Socio-demographics	A
	COVID-19 vaccination status	A&B&C
	Attitude towards COVID-19 booster dose	B&C
	Intention to get COVID-19 booster dose	B&C

A randomized controlled trial will be conducted at Phase II. Questionnaire A will be assigned to the college students at Phase I. Questionnaire B and Questionnaire C will be used to collect grandparents’ information at the beginning and end of Phase II

### Cross-sectional study

Data of the cross-sectional study will be collected via Questionnaire A. Participants will receive a symbolic reward (CNY 1, or USD 0.15) after completing the questionnaire. At this phase, the dependent variable is defined as college students’ willingness to persuade grandparents to receive COVID-19 vaccines. The independent variables are grouped into five blocks:

College students’ socio-demographics: sex, age, ethnic, educational background (junior college students, undergraduate students and graduate students), major and monthly household income.College students’ knowledge of COVID-19 vaccination in older adults included 7 items on a 5-point scale (from “1 = strongly disagree” to “5 = strongly agree”). The variable will be transformed to categorical (No, Yes), with a cut-off value determined by restricted cubic spline.HBM predictor variables for college students’ willingness to persuade grandparents to get COVID-19 vaccination: perceived susceptibility (included 2 items), perceived severity (included 3 items), perceived benefits (included 2 items), perceived barriers (included 1 items) and cues to action (included 3 items). Items in the HBM will be measured on a 1–5 scale (from “1 = strongly disagree” to “5 = strongly agree”). The items of perceived severity and cues to action will be reverse-scored.TPB predictor variables for college students’ willingness to persuade grandparents to get COVID-19 vaccination: attitude (included 1 items), subjective norms (included 3 items) and Perceived Behavioral Control (included 1 item). Items in the TPB will be measured on a 1–5 scale (from “1 = strongly disagree” to “5 = strongly agree”).Grandparents’ socio-demographics: sex, age, educational background, type of residence (urban or rural), cohabitation history (living together with grandchildren for one year or more), living conditions (living alone, only with spouse, with other family members, living in pension institutions), outdoor activities (measured by frequency), chronic disease (having one or more of the following: cardiovascular diseases, diabetes mellitus, tumor, chronic respiratory diseases, liver cirrhosis, chronic renal failure, nervous system diseases and mental disease).

In addition, college students’ willingness to participate in Phase II and grandparents’ actual COVID-19 vaccination status after persuasion will also be included in Questionnaire A to select eligible participants for the next phase.

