## Methods and analysis

### Study design and setting

A combined cross-sectional and experimental study will be conducted online in China to understand college students’ willingness to persuade their grandparents to initiate COVID-19 vaccination and the effect of their persuasion.

The study has two study phases (Fig. 1; Table 1), including a cross-sectional study (Phase I) and a randomized controlled trial (Phase II). Electronic informed consent will be obtained at the beginning of both phases.

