### Inclusion criteria

Individuals who meet the following criteria are eligible at Phase I: (1) college students (junior college students, undergraduate students, graduate students) in mainland China, (2) aged 16 years or older, (3) have at least one living grandparent aged ≥ 60 years who has/have not completed the COVID-19 vaccination recommended by Chinese health authority (including not vaccinated, not completed the initial vaccination series or completed the initial vaccination series but has/have not vaccinated a booster dose).

Those who meet the following criteria are eligible at Phase II: (1) have completed Phase I survey, (2) have the willingness to persuade grandparents to receive COVID-19 vaccines, (3) willing to participate in the follow-up study, (4) have at least one living grandparent aged ≥ 60 years who completed the COVID-19 initial vaccination series but has/have not received a booster dose. Considering that the vaccination status of older adults may change during the time interval between the two phases, eligibility of Phase II will be double-checked by the baseline questionnaire at Phase II (Questionnaire B).

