### Outcomes

At Phase I, the primary outcome is college students’ willingness to persuade grandparents to receive COVID-19 vaccines, measured by the item “Would you like to encourage COVID-19 vaccination for your grandfather/grandmother?” (No, or Yes). In this item, college students were asked to report their intention to encourage COVID-19 vaccination for each of their grandparents. At Phase II, the primary outcome is grandparents’ uptake rate of COVID-19 booster dose, measured by the item “Have you (grandparents) received a COVID-19 booster dose?” (No, or Yes). Secondary outcomes include grandparents’ scores of attitude and intention to get a COVID-19 booster dose.

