### Statistical analysis

All analysis will be performed using R (V.3.6.1, Foundation for Statistical Computing, Vienna, Austria). All effects will be estimated with 95% CI and *P* values. Statistical significance will be taken as two-sided *P* values < 0.05.

According to the types of the variables, descriptive statistical analysis will be carried out for all variables and outcomes, including count, frequency, ratio, mean, standard deviation, and so on. To test the reliability of all the Likert’s scale, Cronbach’s α test will be used.

At Phase I, the primary outcome is college students’ willingness to persuade their grandparents to receive COVID-19 vaccine. Considering that older adults will be nested in families, the condition that all participants are independent, as required for general logistic regression, does not hold. Thus, the multilevel logistic regression model will be necessary. Assuming that each college student has a different intercept, we will apply random intercept, fixed slop models to investigate factors associated with college students’ willingness. The fixed effects will be reported as adjusted odds ratio (AOR) while random effects will be reported by variance, intraclass correlation (ICC). The Akaike’s information criterion (AIC) will be used to determine the goodness of fit.

At Phase II, Chi-squared test will be used for between-group comparison of grandparents’ uptake of COVID-19 booster dose. Incidence rate ratio (IRR) and 95% CIs will be calculated with Poisson regression, adjusted for grandparents’ sex, age, type of residence, educational background, cohabitation history, living conditions, outdoors activities and chronic diseases. Subgroup analyses will be conducted according to grandparents’ sex, age, type of residence, educational background, cohabitation history and chronic diseases. We will use ANCOVA to analyze grandparents’ score of attitude towards COVID-19 booster dose and intention to get a COVID-19 booster dose. Outcomes will be assessed using both intention-to-treat (ITT) and per-protocol (PP) sets. The ITT analysis will calculate outcomes for all enrolled grandparents. The PP analysis will only include grandparents of grandchildren who successfully completed the questions embedded within the health education materials and completed a follow-up survey. To account for loss-to-follow-up, we will use multiple imputation by chained equations to impute missing values.

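### Phase I pools three vaccination states but leaves status out of its covariates, so the pooled willingness cannot answer the question about initiating vaccination, and belief-score odds ratios may be confounded

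*Protocol article*

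**What the plan says.** The article's Study design and setting gives the Phase I question as "willingness to persuade their grandparents to initiate COVID-19 vaccination". Inclusion criteria admits grandparents in three states: "including not vaccinated, not completed the initial vaccination series or completed the initial vaccination series but has/have not vaccinated a booster dose". Under Cross-sectional study, "the dependent variable is defined as college students’ willingness to persuade grandparents to receive COVID-19 vaccines", and Outcomes makes this one answer per grandparent: "college students were asked to report their intention to encourage COVID-19 vaccination for each of their grandparents".

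The covariates are itemised: "The independent variables are grouped into five blocks". They are student socio-demographics, knowledge, Health Belief Model (HBM) scores, Theory of Planned Behavior (TPB) scores, and a grandparent block that begins "Grandparents’ socio-demographics: sex, age, educational background, type of residence (urban or rural), cohabitation history" and ends with chronic disease. Vaccination status appears in none.

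Table 1 and Table 2 both show status collected at Phase I. The stated use is: "grandparents’ actual COVID-19 vaccination status after persuasion will also be included in Questionnaire A to select eligible participants for the next phase". For the model, Statistical analysis says "we will apply random intercept, fixed slop models to investigate factors associated with college students’ willingness". It adds no status term and no stratification for Phase I.

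**The concern.** Encouraging a first dose in someone never vaccinated and encouraging a booster in someone already vaccinated are different acts, but one yes/no item covers both. Two things follow.

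- **The headline proportion.** Initiation concerns grandparents with no dose. A pooled proportion mixes them with booster candidates, who may be the majority.
- **The belief scores.** A grandparent's status can shape what the student believes (perceived barriers, attitude, perceived control) and also whether the student is willing. If so, an adjusted odds ratio for a belief partly reports which dose is outstanding. The student random intercept handles correlation within families. It does not replace a missing grandparent-level covariate.

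Understanding willingness and its associated factors is one of the study's two stated aims, and the Discussion expects the theory models to inform future measures.

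**Working it through.** **1. The plan's own figure.** N = z²p(1−p)/δ², with z = 1.96, p = 0.5 and δ = 0.02, is 3.8416 × 0.25 / 0.0004 = 2401. This matches the article. It is set by the precision of one pooled proportion, so adding status to the model does not change it.

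**2. Are the pooled states small?** The Background gives national coverage at age 60 and over of 89% (any dose) and 84% (full series). That leaves 100 − 89 = 11% unvaccinated and 89 − 84 = 5% part-vaccinated. The boosted share is not given as a percentage, so I assume b = 50% to 70%. Among those not boosted:

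| b | unvaccinated | part-vaccinated | complete, no booster |
|---|---|---|---|
| 50% | 11/50 = 22% | 5/50 = 10% | 34/50 = 68% |
| 70% | 11/30 = 37% | 5/30 = 17% | 14/30 = 47% |

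No state is negligible. A convenience sample of students' grandparents may have a different mix.

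**3. Pooled willingness against group willingness (all willingness inputs assumed).** For simplicity, merge the first two states into one incomplete group, with a share of 32% (b = 50%) or 53.3% (b = 70%).

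- Willingness 80% in the complete group and status odds ratio 0.25: odds 4 × 0.25 = 1, so 50% in the incomplete group. Pooled: 0.32 × 0.50 + 0.68 × 0.80 = 70%, or 0.533 × 0.50 + 0.467 × 0.80 = 64%.
- Willingness 60% and status odds ratio 2: odds 1.5 × 2 = 3, so 75%. Pooled: 0.32 × 0.75 + 0.68 × 0.60 = 65%, or 0.533 × 0.75 + 0.467 × 0.60 = 68%.

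The pooled figure can lie above or below that of the incomplete group. The two agree only if willingness does not depend on status.

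**4. A belief with no association given status.** Let the incomplete share be p₁ among students holding the belief and p₀ among the others. Let willingness be w in the complete group and u in the incomplete group. With status omitted, the odds ratio compares p₁u + (1−p₁)w with p₀u + (1−p₀)w.

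- w = 0.8, status odds ratio 0.25 (u = 0.5), p₁ = 0.45, p₀ = 0.25: 0.665 v 0.725, odds 1.985 / 2.636 = 0.75.
- The same with p₁ = 0.60, p₀ = 0.20: 0.62 v 0.74, odds 1.632 / 2.846 = 0.57.
- w = 0.6, status odds ratio 2 (u = 0.75), p₁ = 0.60, p₀ = 0.20: 0.69 v 0.63, odds 2.226 / 1.703 = 1.31.

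Across w = 60% or 80%, status odds ratios 0.25, 0.5 and 2, and both unequal pairs of shares, the range is 0.57 to 1.31. It is exactly 1.00 if p₁ = p₀ or if the status odds ratio is 1. The calculation is single-level and omits the other covariates.

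**The case against.** The strongest objection concerns the causal order. Status does not cause a grandparent's age, and it is not a plausible cause of the listed chronic diseases. The likely order is age or illness, then status, then willingness. Status is then a mediator, and the model without it estimates an overall association, which is a legitimate target for a study of associated factors. This stands.

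A reader might still infer that the age and chronic disease results would be false positives, and might support that by simulation. Suppose 45% v 20% are unvaccinated at age 80 and over v younger, with a status odds ratio of 0.37, an assumed willingness of 70% among the vaccinated, and no age effect given status. Willingness among the unvaccinated is then 46.3%. The age groups have 0.45 × 0.463 + 0.55 × 0.70 = 0.594 and 0.20 × 0.463 + 0.80 × 0.70 = 0.653, an odds ratio of about 0.78. That is the true overall age association in such data. Frequent significance would be power to detect it, not error.

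Other points on that side:

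- Some of the status effect may be carried by covariates already planned, such as perceived barriers. This stands, and is one reason why the size is unknown.
- The article does not say that status is used only for selection, and it promises descriptive statistics for all variables. Describing status alone, however, does not give willingness by status.
- Details may sit in an analysis plan that is not shown. But the article itself itemises the covariates, so the omission is a stated choice.
- The operative outcome wording covers any dose, so the reference to initiating could be loose phrasing. It is nevertheless how the Phase I question is put in both the Background and Study design and setting.

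**Conclusion.** The point holds within limits. Phase I pools three vaccination states and omits status from an itemised covariate list. The pooled willingness figure therefore cannot answer the question about initiating vaccination. The HBM and TPB odds ratios can be confounded by the outstanding dose.

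The documents fix neither the size nor the direction. The 0.57 to 1.31 range is illustrative, and there is no distortion of a null factor if status is unrelated to the belief or to willingness. That a grandparent's status precedes the student's beliefs is also an assumption, which a cross-sectional survey cannot settle. The documents do not support calling the age and chronic disease results biased.

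Only the Phase I willingness results are touched. Phase II restricts to grandparents with a complete series and no booster, so it is unaffected, as are both sample sizes.

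**What to change.** 1. Report willingness separately for the three groups: unvaccinated, initial series incomplete, and series complete without booster.
2. Fit the Phase I multilevel model twice, without and with status as a three-level grandparent-level fixed effect (2 degrees of freedom). Read the first as overall associations and the second as associations given the outstanding dose. The two odds ratios can differ without confounding, so a difference alone does not prove it.
3. Use the status that established Phase I eligibility. Clarify the Cross-sectional study wording that describes the Questionnaire A status as recorded after persuasion. Status after persuasion could be a consequence of willingness, and adjusting for it could itself distort the odds ratios.
4. Confirm that Questionnaire A keeps the three-level eligibility status for each grandparent. If it does, this is a change to the analysis text only.

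The cost is two parameters, one extra model and a three-row table. The rows will be less precise than the pooled ±2 points. With one grandparent per student, p = 0.5 and the mix in the working, the unvaccinated row has 0.22 × 2401 = 528 to 2401 × 11/30 = 880 answers, a half-width of 1.96 × √(0.25/n) = 4.3 to 3.3 points. The part-vaccinated row has 240 to 400 answers, or 6.3 to 4.9 points.

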### Sample size

At Phase I, we use the formula $$N=\frac{{Z}_{\text{1-}\alpha }^{2}\times p\times (1-p)}{{\delta }^{2}}$$ to calculate the sample size. Given an alpha value of 0.05 and the permissible error δ of 0.02, assuming the proportion of college students willing to recommend vaccination for older adults at home as 50%, a minimum of 2401 subjects are required for this quantitative survey.

At Phase II, we use the formula $$N=\frac{[{Z}_{1-\alpha /2}\times \sqrt{\bar{p}\times \bar{q}\times (1+\frac{1}{k})}+{Z}_{1-\beta }\times \sqrt{{p}_{1}\times {q}_{1}+\frac{{p}_{2}\times {q}_{2}}{k}}{]}^{2}}{({p}_{1}-{p}_{2}{)}^{2}}$$ to calculate the sample size. Using parameter, the rate of booster vaccination in older adults is 2.5%, [23, 24] and this figure is expected to increase to 4 times after information intervention, [25] which requires a sample size of 162 eligible older adults in each group to achieve 80% power at a 2-sided 5% level of significance to detect a net difference. Through the preliminary data in Phase I, at least 101 eligible college students are needed to provide the required sample size of eligible older adults.

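### Phase I splits the knowledge score at a spline-derived cut-off, which loses at least about a third of its information if the effect is linear and, depending on an unstated rule, can raise its type I error

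*Protocol article*

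**What the plan says.** In the protocol article, the section Cross-sectional study describes the knowledge scale, which "included 7 items on a 5-point scale", and then fixes its handling: "The variable will be transformed to categorical (No, Yes), with a cut-off value determined by restricted cubic spline". It gives no cut-off value, number of knots, reference value or feature of the curve at which the cut is to be read. No such split is stated for the Health Belief Model and Theory of Planned Behavior items.

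The same section names one outcome for this phase: "the dependent variable is defined as college students’ willingness to persuade grandparents to receive COVID-19 vaccines". The section Outcomes makes it a No/Yes answer for each grandparent.

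The section Statistical analysis applies "random intercept, fixed slop models to investigate factors associated with college students" and their willingness, reporting adjusted odds ratios (AORs). For all analyses, "Statistical significance will be taken as two-sided *P* values < 0.05". It describes no allowance for a data-derived cut, no validation sample and no analysis of the continuous score.

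The only earlier data mentioned, in Data collection, are a pre-survey of 30 students. It served to revise the questionnaires and the protocol, and nothing says that it set a cut-off.

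**The concern.** A restricted cubic spline has no cut-off of its own. One appears only after the spline has been fitted to an outcome and some point on the curve has been chosen. The outcome named for Phase I is willingness and no outside data set is mentioned, so the natural reading is that the students who supply the cut also supply the test.

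Two things follow. First, any No/Yes split treats all scores on one side of the cut as equal, so it gives up information about a graded effect. Second, if the cut is placed where the fitted curve happens to separate willing from unwilling students, the later 5% test takes no account of that choice.

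At stake is the AOR for knowledge, together with its interval and P value. Finding factors associated with willingness is a stated aim of Phase I, and knowledge is one of the five blocks of predictors.

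**Working it through.** **The plan's own figure.** With p = 0.50, δ = 0.02 and two-sided α = 0.05: N = 1.96² × 0.5 × 0.5 / 0.02² = 2400.9, so 2401, as stated in Sample size. This N was set for estimating a proportion. The article gives no figure for the split score.

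**Information kept by a split.** If the effect is linear in the score, the share of information kept is the squared correlation between the score and its No/Yes version. For a normal score with a share q below the cut c, this is φ(c)² / [q(1 − q)]. At the median: 0.3989² / 0.25 = 0.637. The last column multiplies the share kept by 2401.

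| Split | Kept | Lost | Equivalent number of students |
|---|---|---|---|
| 50/50 | 0.637 | 36% | 1529 |
| 40/60 | 0.622 | 38% | 1493 |
| 30/70 | 0.576 | 42% | 1383 |
| 20/80 | 0.490 | 51% | 1176 |
| 10/90 | 0.342 | 66% | 821 |

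A simulated sum of seven correlated 1–5 items (range 7–35, mean 24.8, SD 5.7; summing is an assumption) behaves similarly. It keeps 0.673 at the cut nearest the median (33% lost), 0.635 with 73% at or above the cut (36% lost), 0.555 with 82% (45% lost) and 0.451 with 23% (55% lost).

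**Type I error.** The setting has no association, n = 2401 and 4000 replicates per cell. The proportion willing is 50% (Sample size) or 80% (an assumption), and the spline has 3, 4 or 5 knots (an assumption). A spline logistic model is fitted, the cut is read between the 5th and 95th percentiles of the score, and the split is tested in the same data at two-sided 5%. If the curve crosses the average log-odds more than once, the steepest crossing is used; if it has no turning point, the steepest point is used. Entries are rejection percentages at 50% / 80% willing.

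| Rule for the cut | 3 knots | 4 knots | 5 knots |
|---|---|---|---|
| None: score kept linear | 5.8 / 5.2 | 4.9 / 5.3 | 4.5 / 4.5 |
| Median (as when a median reference sets the odds ratio to 1) | 5.7 / 5.2 | 5.6 / 5.5 | 4.9 / 5.1 |
| Curve crosses average log-odds | 9.1 / 8.6 | 10.1 / 10.3 | 12.5 / 12.1 |
| Steepest point | 8.5 / 8.2 | 11.8 / 10.9 | 12.3 / 13.1 |
| Turning point | 2.4 / 2.2 | 1.3 / 1.4 | 1.1 / 1.1 |

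The first two rows do not use the spline, so their columns differ only by simulation noise. The Monte Carlo standard error is √(0.05 × 0.95 / 4000) = 0.34 points at 5% and √(0.10 × 0.90 / 4000) = 0.47 points at 10%.

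The pattern has a simple reason. A mean-crossing or steepest-point cut lines the split up with a chance rise or fall in the curve. A turning-point cut puts similar parts of the curve on both sides and blunts the contrast.

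**The case against.** The strongest reply is that the article is a condensed account. The knots, the reference value and the rule for reading the cut may stand in a fuller document, and under two plausible rules the type I error is not raised. That stands, and it is why the inflation can only be put as a possibility. It does not answer the loss of information, because splitting the score is itself a stated choice and the loss arises under every rule if the effect is graded.

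It is also fair to say that use of the same data is inferred. No sentence says so; it is the natural reading because no other source for the cut is named. And if willingness truly jumped at one score, a split at that score would lose little. Nothing in the article argues for such a jump, and a spline term would follow it closely enough.

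A reader might infer more than the documents support:

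- **That false positives will be inflated and the AOR pushed away from 1.** This needs an outcome-read cut of the mean-crossing or steepest-point kind, which the article does not specify. With a median cut the likelier error is to miss a real association.
- **That the two harms add up at the sizes given.** The 33–36% loss belongs to a cut near the median, where the type I error stays near 5%. The information lost at the spline-read cuts was not calculated.
- **That every cut will be searched for the strongest result.** In the same simulations this gave 34–37% false positives, but the article does not propose it.
- **That the trial is compromised.** The content of the Phase II education package is already laid out in Table 3 and does not wait on the knowledge AOR.

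**Conclusion.** The point holds as a limited one that is worth correcting. Given a linear effect, the planned split wastes at least about a third of the information on knowledge, and roughly 40–65% if the cut falls clearly off centre. The type I error for this one predictor could lie anywhere from about 1% to 13% according to a rule the article leaves open, with about 8–13% under the two unfavourable readings.

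The information figures assume a linear effect and either a normal or a summed Likert score. The error rates assume independent students and no covariates, unlike the planned adjusted multilevel model, so they show direction and rough size only. The Phase I proportion willing, the sample size of 2401 and the Phase II randomised comparison are untouched.

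**What to change.** Replace the sentence on dichotomising with one that keeps the knowledge score continuous in the multilevel logistic model. It can enter as a linear term, or as the restricted cubic spline already planned, with the number and position of knots set beforehand, a joint test of all its terms for the association and a test of non-linearity. The effect can be reported as the AOR between the 25th and 75th percentiles of the score. If a No/Yes version is wanted, use it for description only, with a cut fixed in advance without reference to the outcome data.

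The cost is one sentence and no extra data. The small drawback is that a spline effect is slightly harder to report than a single Yes/No odds ratio.
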